**Fig. 2 Fig2:**
[figure not shown]
Fibrinogen Early In Severe Trauma studY (FEISTY) Standard Protocol Items: Recommendations for Interventional Trials (SPIRIT) flowchart

**Table 2 Tab2:** Outcome measures

Primary outcome measures:	
1. (A) Time to administration of fibrinogen administration (FC or Cryo) from time of ROTEM® analysis and clinical scenario suggesting that fibrinogen supplementation is required	
1. (B) Feasibility of administering FC within 30 min of ROTEM® and clinical scenario suggesting that fibrinogen supplementation is required	
2. Effects of fibrinogen supplementation (FC and Cryo) on fibrinogen levels as measured by FIBTEM and Clauss Fibrinogen (FibC)	
Secondary outcome measures:	
1. Transfusion requirements (in number of units) of PRBC, FFP, FC, Cryo, platelets, PCC at 4, 6, 12, 24 and 48 h	
2. Duration of bleeding episode or time until surgical haemorrhage control with no further coagulation factors	
3. Duration of mechanical ventilation	
4. Duration of ICU and hospital LOS	
5. ROTEM® (Sigma and Delta), Multiplate®, FBC, INR, APTT, FibC analysis at prespecified time points	
6. Evaluation of EXTEM CT in response to fibrinogen supplementation	
7. Adverse events: TACO, TRALI, Sepsis, MOF	
8. Thromboembolic complications	
9. All-cause mortality at 4, 6, 24 h and up to 90 days	
Feasibility outcome measures:	
1. Transfusion requirements (in number of units) of PRBC, FFP, FC, Cryo, Platelets, PCC at 4, 6, 12, 24 and 48 h	
2. Duration of bleeding episode or time until surgical haemorrhage control with no further coagulation factors	
3. Duration of mechanical ventilation	
4. Duration of ICU and hospital LOS	
5. ROTEM® (Sigma and Delta), Multiplate®, FBC, INR, APTT, FibC analysis at prespecified time points	
6. Evaluation of EXTEM CT in response to fibrinogen supplementation	
7. Adverse events: TACO, TRALI, Sepsis, MOF	
8. Thromboembolic complications	
9. All cause mortality at 4, 6, 24 h and up to 90 days	
Feasibility outcome measures:	
1. Time to randomisation	
2. FC and Cryo wastage	
3. Proportion of patients with blood sampling at all prespecified time points	
4. Number of missed patients (eligible but not enrolled)	
5. Randomisation errors	
6. Protocol violations	

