### Blood sampling

As previously stated the requirement for fibrinogen supplementation will be guided by FIBTEM A5 (ROTEM® Sigma) analysis. A number of other blood tests to assess haemostasis will be performed at predefined time points from admission to day 7 (Fig. 2). These include: ROTEM® Sigma and Delta (FIBTEM, EXTEM, INTEM, HEPTEM), Multiplate® (ADP, ASP, TRAP), TEG 6S (CK, CKH, CRT, CFF), haemoglobin, platelet count, International Normalised Ratio (INR), Activated Partial Thromboplastin Time (APTT), Clauss Fibrinogen. Arterial blood gas analysis (pH, lactate, base deficit, HCO_3_
^−^) will be performed on admission and as clinically indicated. Likewise, blood chemistry results assessing organ function will be performed at the discretion of the treating clinical staff.

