### Statistical analysis

Data analyses will be performed with a coded binary treatment indicator to preserve blinding to treatment allocation until the trial report is finalised by the writing committee. The trial primary and main secondary outcomes will be reported using intention-to-treat analyses based on all randomly assigned patients, except any who withdraw consent for use of all trial data.

Baseline variables will be summarised using descriptive statistics. The trial primary outcome and other time-to-event outcomes will be displayed as Kaplan-Meier curves and compared between treatments with Cox proportional hazards regression including, as covariates, the trial site stratification factor and patient age and sex. Sensitivity analyses will be performed using unadjusted Cox models which include a binary indicator of treatment as the only covariate, and also using multivariable Cox models including any other baseline covariates exhibiting substantial imbalance between randomisation arms. Lack of proportionality in any Cox model on testing will result in that outcome being assessed using a log-rank test and summarised using the Kaplan-Meier estimated median time to event [34]. Other secondary analyses, including assessment of the differential proportion of thromboembolic complications and mortality at specified time points, will be compared using either chi-square or Fisher exact tests, and also using logistic regression adjusting for the same covariates used in the Cox models. Results will be summarised using frequency tables, and risk ratios or odds ratios as appropriate, with 95% confidence intervals. Approximately normally distributed continuous variables (either untransformed or following log or other normalising transformation) will be compared using *t* tests, or otherwise compared using nonparametric methods (Mann-Whitney).

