The differential trajectory of fibrinogen levels over time according to intervention will be assessed with fibrinogen measurements at predefined time points for each patient. Initial exploratory analyses will be conducted using a ‘summary measures’ approach [35], comparing maximum and minimum fibrinogen levels within individual patients during the acute resuscitation phase and also the maximum fibrinogen in the postresuscitation phase. Subsequently, univariable and adjusted multivariable linear regression analyses will be used to assess the differential effects on circulating fibrinogen levels of treatment allocation using a generalised estimating equation (GEE) approach with robust error estimates to account for the within-subject correlation of fibrinogen levels over time [36].

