There is growing evidence to support the use of VHA to rapidly guide targeted factor replacement in traumatic haemorrhage but data from RCTs is limited [41, 42]. A recent, single-centre RCT has reported significant reductions in blood product transfusion and improved survival with a VHA-guided MHP [43]. Whilst the evidence of a positive impact on mortality is equivocal, it is clear that VHA can be used to rapidly and reliably identify coagulopathic trauma patients [44, 45]. The FIBTEM assay can be utilised as a marker of TIC, predict massive transfusion and it correlates well with standard laboratory measures of fibrinogen concentration [11, 46, 47]. The present study will utilise the FIBTEM assay to identify patients with hypofibrinogenaemia and subsequently guide dosing of FC and Cryo. The FIBTEM A5 will be used to permit rapid intervention [48]. Each of the trauma centres involved in the trial have varying degrees of experience with VHA use in severe trauma [49]. This trial will utilise the ROTEM Sigma device (an automated cartridge-based system) to evaluate FIBTEM A5 and guide subsequent fibrinogen replacement. The location of the device either, at the point of care (POC) or in the laboratory environment, will depend on local logistical considerations and will be decided by each individual centre. Other blood product components will be administered as per each individual trauma centre’s standard MHP. Specifically, the use of tranexamic acid (TXA) as an intervention for hyperfibrinolysis will be as per standard practice at each individual trauma centre. The majority of Australian trauma centres are currently participating in the randomised controlled PATCH trial, investigating the prehospital use of TXA in severely injured trauma patients likely to have TIC [50]. Co-enrolment in PATCH and FEISTY has been agreed by both trial teams.

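### Continuous secondary outcomes are compared by unadjusted t or Mann-Whitney tests, although the Cox and logistic models adjust for site, age and sex; precision is lost, but no bias arises

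*Protocol article*

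**What the plan says.** All references are to the protocol article.

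- **Continuous variables (Statistical analysis).** If approximately normal, as they stand or after transformation, they "will be compared using *t* tests, or otherwise compared using nonparametric methods (Mann-Whitney" being the alternative named. No covariate and no adjusted counterpart is given.
- **Time-to-event outcomes (same section).** These are compared by "Cox proportional hazards regression including, as covariates, the trial site stratification factor and patient age and sex". Unadjusted Cox models are kept as sensitivity analyses.
- **Binary outcomes (same section).** These are compared by chi-square or Fisher tests, and "also using logistic regression adjusting for the same covariates used in the Cox models".
- **Fibrinogen levels (same section).** After a summary-measures step, "univariable and adjusted multivariable linear regression analyses will be used to assess the differential effects on circulating fibrinogen levels", by GEE. This model is planned for fibrinogen only.
- **Outcomes affected (Table 2).** Transfusion units at 4 to 48 h (secondary outcome 1); the non-fibrinogen part of the ROTEM, Multiplate, blood count and clotting panel (5); and "Evaluation of EXTEM CT in response to fibrinogen supplementation" (6). Durations can be read as time-to-event outcomes and are left aside here.
- **Admission values (Blood sampling).** "A number of other blood tests to assess haemostasis will be performed at predefined time points from admission to day 7".
- **Why sites may differ (Discussion).** "Other blood product components will be administered as per each individual trauma centre’s standard MHP". Experience with viscoelastic testing and the location of the device also vary by centre.

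**The concern.** Three classes of outcome get an adjusted analysis and one does not, and no reason is given. Two pieces of information already in hand are then poorly used.

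1. **Site.** If allocation is balanced within site and site predicts the outcome, the arms are more alike than the plain t test assumes. Its standard error is too large and its true type I error falls below 5%. Blood-product practice follows local protocols, so a site effect on units given is plausible.
2. **Admission value.** For EXTEM CT and the other non-fibrinogen tests a pre-treatment value is scheduled. ANCOVA would use it; a two-group test of post-dose values does not, and a test of change scores uses it less efficiently.

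At stake is the precision of the secondary comparisons in a trial of 100 patients whose results are meant to inform a larger trial addressing transfusion requirements and mortality.

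**Working it through.** **The plan's own figure.** Sample size section: 50 per arm, SD 14 min, difference 8 min, two-sided 5%. With √(2/50) = 0.2:

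- power = Φ(8/(14 × 0.2) − 1.96) = Φ(2.857 − 1.96) = 81.5% (80.8% by noncentral t), against a stated value of about 80%;
- detectable difference = 2.80 × 14 × 0.2 = 7.8 min, and 2.80 × 30 × 0.2 = 16.8 min, against the stated 8 and 17.

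These reproduce. They belong to the primary outcome; the article states no power for any continuous secondary outcome. As a neutral benchmark I therefore take the effect that gives exactly 80% unadjusted power with 50 per arm: 2.80 × 0.2 = 0.56 SD.

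**Assumed inputs.** The article gives neither the between-site share of variance (s) nor the correlation of admission and later values (ρ), so ranges are shown.

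**Site in the model.** The residual SD is multiplied by √(1 − s), and power = Φ(2.80/√(1 − s) − 1.96). If allocation is balanced within site, the plain t test has true type I error 2[1 − Φ(1.96/√(1 − s))] and power Φ(0.842/√(1 − s)).

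| s | interval width ratio | power, site in model | power, plain t | type I error, plain t |
|---|---|---|---|---|
| 0 | 1.00 | 80% | 80% | 5.0% |
| 5% | 0.97 | 82% | 81% | 4.4% |
| 10% | 0.95 | 84% | 81% | 3.9% |
| 20% | 0.89 | 88% | 83% | 2.8% |

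A simulation with assumed site sizes 40/30/20/10, balanced within site (4,000 runs per setting), agrees. At s = 5%, 10% and 20% the plain t test had type I error 4.3%, 4.2% and 2.9%, against 4.8%, 5.5% and 5.2% with site in the model. At s = 10% simulated power was 80.6% plain and 83.1% adjusted; at s = 20% it was 81.8% and 87.1%. The Monte Carlo standard error at 5% is √(0.05 × 0.95/4000) = 0.34 points, so only the 20% row departs clearly from nominal. The gain from site is about 3 points at s = 10% and 5 at s = 20%.

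**Admission value in the model (laboratory outcomes only).** In units of the outcome SD, with equal variance before and after dosing, the SD is 1 for raw post-dose values, √(2(1 − ρ)) for change scores and √(1 − ρ²) for ANCOVA. Power = Φ(2.80/SD − 1.96).

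| ρ | raw post-dose | change score | ANCOVA | ANCOVA width ratio vs raw |
|---|---|---|---|---|
| 0.3 | 80% | Φ(2.37 − 1.96) = 66% | Φ(2.94 − 1.96) = 84% | 0.95 |
| 0.5 | 80% | Φ(2.80 − 1.96) = 80% | Φ(3.23 − 1.96) = 90% | 0.87 |
| 0.7 | 80% | Φ(3.62 − 1.96) = 95% | Φ(3.92 − 1.96) = 98% | 0.71 |

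ANCOVA would match the raw comparison of 100 patients with 100(1 − ρ²) = 91, 75 or 51 patients.

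**The case against.** The strongest case against is that nothing here is an error. The unadjusted test is valid, if anything conservative, and the outcomes are secondary in a self-described exploratory pilot. Fibrinogen level, which Table 2 lists among the primary outcomes, already has an adjusted model. That is right, and it limits the point to efficiency and consistency.

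Several stronger readings are tempting, and the article does not support them:

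- **That a baseline is ignored for transfusion units.** They have no pre-treatment value. Only site, age and sex apply, so the 84% to 98% ANCOVA figures do not concern them.
- **That raw post-dose EXTEM CT is what will be tested.** The article does not say so. Measured as a response, it may mean change, which already uses the earlier value. The ANCOVA gain at ρ = 0.7 is then 95% to 98%, not 80% to 98%. At ρ = 0.5 or below, change scores do no better than raw values.
- **That all intervals are too wide.** This holds for the t-test branch. The article attaches no interval to Mann-Whitney, where skewed unit counts would probably go; there the cost is power.
- **That the larger trial would be mis-sized.** The choice of test does not fix the variance used for planning. Within-site variance can be computed from the same data, and total SD is a legitimate, conservative input.
- **That chance baseline imbalance biases the comparison.** Its standard error already allows for that.

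It is also fair that 50 per arm may be too many for EXTEM CT response, since patients are randomised on arrival but dosed only at the FIBTEM threshold with significant haemorrhage. The power figures are benchmarks, not predictions.

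What remains is a stated analysis that uses the data less well than its neighbours in the same section. It is a choice the article makes, not a detail it leaves open.

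**Conclusion.** The point holds as a loss of precision, not as bias or invalid inference. For transfusion units the plain test leaves out the stratification factor. For EXTEM CT and the non-fibrinogen haemostasis tests it also makes no efficient use of the admission value.

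The site effect is small unless centres differ strongly, reaching about 5 points of power when site explains 20% of the variance and nothing when it explains none. The admission value matters more: against raw post-dose values it is worth about 10 points at a correlation of 0.5.

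These sizes rest on assumed site shares and correlations, a borrowed 80% benchmark, 50 evaluable patients per arm, and allocation balanced within site. On the last, the Statistical analysis section names site as the stratification factor, while the Randomisation section mentions only blocks and unequal recruitment across sites. The change is worth making because it costs little.

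**What to change.** In the Statistical analysis section, or in the SAP:

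- **Continuous secondary outcomes.** Add a linear model, transformed where needed, with treatment, site, age and sex. For EXTEM CT and the other non-fibrinogen laboratory measures, add the admission value.
- **Transfusion units.** Use a count model with treatment, site, age and sex, or a site-stratified rank test (van Elteren). A log-scale linear model suits counts with many zeros poorly.
- **Reporting.** Give the adjusted estimate with its 95% CI as the main result. Keep the t and Mann-Whitney tests as unadjusted sensitivity analyses, as the Cox plan already does.

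The cost is wording. Site, age, sex and admission samples are already in the plan. With four sites the model spends 3 + 1 + 1 = 5 further degrees of freedom, or 6 with the admission value, out of 98. A simple rule is needed for patients without an admission sample so that they stay in the analysis.

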Regardless of which approach is used fibrinogen can be replaced with plasma, cryoprecipitate (Cryo) and fibrinogen concentrate (FC) each containing different amounts of fibrinogen; 2 g/L, 8–16 g/L and 20 g/L, respectively. The low concentration of fibrinogen in plasma and the large volumes required potentially make it unsuitable for dedicated fibrinogen supplementation [23–25]. The RETIC trial (NCT01545635) comparing plasma to factor concentrate-based resuscitation has recently been terminated early after an interim analysis revealed potential harm to patients randomised to the plasma arm. Cryoprecipitate contains substantially higher concentrations of fibrinogen than plasma and is widely accepted as the standard of care for fibrinogen supplementation in severe haemorrhage [26]. However, its use is not currently supported by high-level evidence [27]. The CRYOSTAT trial reported in 2015 that early fibrinogen supplementation utilising Cryo was feasible and effectively maintained fibrinogen levels in traumatic haemorrhage [28]. The use of FC has a number of theoretical advantages including: standard dose per vial, reduced volume, viral inactivation, no requirement for ABO compatibility matching, ease of reconstitution and administration. However, in severe trauma there are no robust clinical trials to demonstrate a survival or cost-effectiveness benefit compared to Cryo [6, 25, 29].

A number of key questions regarding fibrinogen supplementation in traumatic haemorrhage remain unanswered, including: (1) What tests, if any should be utilised to guide fibrinogen therapy? (2) What is the optimal product for fibrinogen replacement? (3) What is the optimal dose of fibrinogen? and (4) What is the impact of early fibrinogen replacement on clinically important outcomes?

The objectives of this trial are to assess the feasibility of early fibrinogen replacement utilising FC compared to the use of Cryo in patients with traumatic haemorrhage and viscoelastic evidence of hypofibrinogenaemia. We hypothesise that fibrinogen replacement to reverse hypofibrinogenaemia in traumatic haemorrhage may be achieved more rapidly, and with a more predictable dose response, using FC compared to Cryo.

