### Intervention

After compliance with consent requirements and with the treating clinician’s approval, patients will be randomised to receive fibrinogen supplementation using either FC (Riastap®, CSL Behring GmbH, Marburg, Germany) or Cryo (Australian Red Cross Blood Service). The requirement for fibrinogen supplementation will be defined by a FIBTEM A5 (clot amplitude 5 min after clot formation) ≤10 mm together with a clinical scenario suggesting significant haemorrhage. The intervention will be performed in randomised patients as soon as possible after each FIBTEM threshold result becomes known. Patients will remain in their allocated intervention arm for the duration of their hospital admission up to 30 days. Dosing of FC and Cryo will be guided by the FIBTEM A5 result as per trial protocol (Fig. 1). FC will be administered by intravenous injection and Cryo by rapid intravenous infusion. Fibrinogen supplementation will be continued throughout the resuscitation according to protocol and as per the allocated intervention arm (Fig. 1).

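### Fibrinogen level contrasts compare two strategies titrated to one FIBTEM trigger, so alone they attenuate any product difference and do not answer the dose-response question

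*Protocol article*

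**What the plan says.** **Dosing (Protocol article, Intervention).** One trigger serves both arms: "The requirement for fibrinogen supplementation will be defined by a FIBTEM A5 (clot amplitude 5 min after clot formation) ≤10 mm", together with a clinical picture of significant haemorrhage. The size of the dose also follows the assay: "Dosing of FC and Cryo will be guided by the FIBTEM A5 result as per trial protocol". Dosing repeats: "The intervention will be performed in randomised patients as soon as possible after each FIBTEM threshold result becomes known", and "Fibrinogen supplementation will be continued throughout the resuscitation according to protocol and as per the allocated intervention arm".

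**Analysis (Protocol article, Statistical analysis).** The first step is a summary-measures analysis "comparing maximum and minimum fibrinogen levels within individual patients during the acute resuscitation phase", plus the maximum after resuscitation. Regression models then "assess the differential effects on circulating fibrinogen levels of treatment allocation using a generalised estimating equation (GEE) approach". That section names no change after the first dose, no response per gram and no amount given.

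**Question (Protocol article, Background, Table 2 and Discussion).** The hypothesis is that replacement can be achieved faster and "with a more predictable dose response, using FC compared to Cryo". Table 2 lists the effect on fibrinogen levels, by FIBTEM and Clauss, as primary outcome measure 2. The Discussion expects the trial to inform dosing. Units of FC and Cryo at 4 to 48 h are a separate secondary outcome.

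**The concern.** FIBTEM A5 is both the signal that triggers and sizes treatment and one of the two measures of its effect. If one product raises A5 less per gram, its patients stay at or below the threshold more often and receive more. The level difference then shrinks while a difference in grams grows. Clauss fibrinogen does not trigger doses, but the Discussion says FIBTEM correlates well with laboratory fibrinogen, so it should be affected too.

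The stake is interpretation. Table 2 gives the level outcome primary rank, and the Background and Discussion ask about dose response and dosing. A small level difference could come from two products that act alike, or from two that act differently with one given in larger amounts. The planned level contrasts cannot tell these apart.

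**Working it through.** **1. The plan's own figure.** The only power statement concerns time to fibrinogen: SD 14 min, difference 8 min, 50 per arm, two-sided 5%. The standard error is 14 × √(2/50) = 2.8 min, 8/2.8 = 2.86, and 2.86 − 1.96 = 0.90, giving power of 81.5% (80.8% by noncentral t) against the stated 80% or so. It reproduces, but has no bearing on levels, for which no figure is given.

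**2. Inputs for the level question.** From the documents: trigger A5 ≤10 mm in both arms, repeat dosing, and a rise of 1–2 mm FIBTEM per gram (Discussion). That range is given for FC and Cryo together; assigning different values to the two arms is an assumption made here to see what the analysis would show if they differed. Dose steps, re-test interval, ongoing loss and starting A5 are also assumed.

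**3. First simulation (200,000 per arm).** Starting A5 is about 8 mm (SD 2, limited to 2–10). Every patient gets a first dose, then another whenever measured A5 is ≤10 mm, over six cycles. Grams per dose = (12 − measured A5)/1.5, rounded up, at least 1. New A5 = old A5 + response × grams + noise (SD 1 mm) − loss. Measurement SD is 1 mm.

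| Loss per cycle (mm) | Response (mm/g) | Difference after first dose (mm) | Difference at last cycle (mm) | Last cycle, no re-dosing (mm) | Grams, stronger v weaker |
|---|---|---|---|---|---|
| 0.5 | 1.5 v 1.0 | 1.64 | 0.78 | 1.65 | 5.10 v 6.88 |
| 1.0 | 1.5 v 1.0 | 1.65 | 0.80 | 1.61 | 6.39 v 8.80 |
| 1.5 | 1.5 v 1.0 | 1.64 | 0.88 | 1.39 | 7.94 v 11.03 |
| 0.5 | 2.0 v 1.0 | 3.27 | 1.57 | 3.28 | 4.24 v 6.87 |
| 1.0 | 2.0 v 1.0 | 3.28 | 1.54 | 3.24 | 5.16 v 8.79 |
| 1.5 | 2.0 v 1.0 | 3.28 | 1.65 | 2.93 | 6.34 v 11.03 |

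Relative to the first-dose difference, 46% (1 − 0.88/1.64) to 53% (1 − 1.54/3.28) is lost by the last cycle. Relative to the same cycle without re-dosing, the loss is 37% (1 − 0.88/1.39) to 53% (1 − 0.78/1.65). The weaker product uses 1.35 to 1.74 times the grams. The first-dose rise per gram keeps the whole difference: for example 1.30 v 0.80 mm/g where the truth differs by 0.5, and 1.62 v 0.62 mm/g where it differs by 1.0.

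**4. Second simulation.** Starting A5 is 3–10 mm, with 3 g fixed or 2–5 g graded per trigger and a loss of 0.5–1.0 mm per half hour. At 2 v 1 mm per gram:

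- difference after the first dose: 3.0–3.3 mm
- difference at 4 h: 1.3–1.7 mm
- difference in within-patient maximum: 1.8–2.5 mm
- difference in within-patient minimum: 0.1–0.2 mm
- grams: 4.4–5.9 v 7.4–9.9

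At 1.8 v 1.2 mm per gram, 1.8–2.0 mm falls to 0.7–1.0 mm at 4 h. The minimum was the pre-treatment value in 67–96% of patients. That result needs the pre-dose sample to count as part of the resuscitation phase; in the first simulation, which left it out, the minimum differed by 0.57–1.97 mm.

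**5. A remedy that fails.** Using every sample taken before a second dose was tested at 2 v 1 mm per gram. At 4 h, 25–66% of the stronger arm but only 2–14% of the weaker arm were still before a second dose. The restricted contrast was 1.4–2.0 mm against a true 3.0–3.5 mm, because the weaker arm keeps only its good responders.

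**The case against.** The strongest reply is that nothing here is an error. The GEE by allocation estimates the effect of assignment to one titrated strategy or the other, and is valid for that. The amount given is already a secondary outcome. The Trial endpoints section makes time the primary outcome and treats effects on plasma fibrinogen as hypothesis-generating. The hypothesis concerns speed and predictability, not a larger mean rise per gram. A dose-response analysis could sit in an analysis plan that is not shown.

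Much of this stands: the GEE should stay, and the amount given would be reported. But units of FC and Cryo are not a common scale (the Discussion equates 3–4 Cryo units with 1 g), and no stated analysis ties amount to level. Predictability of response is itself a dose-response property that titrated levels do not measure. The point rests on the contrasts the article does specify, and Table 2 does list levels as primary.

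A reader might go further and infer that re-dosing makes the arms converge and hides the difference, or that a null result would be reported as equal effect. The documents support neither. In every simulated setting a level difference in the same direction remained. In the first simulation the mean level over six cycles still differed by 0.99–1.02 mm at 1.5 v 1.0 mm per gram, with power of at least 99% at 50 dosed patients per arm. The article states no equivalence claim or margin, so misreading is a risk, not a plan.

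**Conclusion.** The point holds as attenuation. Shared A5-triggered re-dosing makes the maximum, minimum and GEE contrasts comparisons of two titrated strategies, which understate a difference in response per gram if there is one. Under the assumed settings roughly 40–55% of the level difference is gone by the end of the period, and the weaker product is given in amounts about 35–74% larger. The within-patient minimum says least where it includes the pre-dose sample. The direction follows from the text. The sizes do not: they depend on the undisplayed dosing figure, on assumed bleeding loss and on an assumed difference between products that the article does not assert. The change is worth making because the stated hypothesis and Table 2 need an answer that the level contrasts alone cannot give.

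**What to change.** Keep the by-allocation GEE and label it the intention-to-treat comparison of the two strategies. Then:

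- **Add a product-effect analysis:** change from the pre-dose sample to the first sample after the first dose, for FIBTEM A5 and for Clauss where sampled, adjusted for pre-dose level and expressed per nominal gram. Compare both its mean and its variability between arms, since predictability is the hypothesis.
- **Report the amount given** beside the trajectories: number of doses and cumulative nominal grams of fibrinogen, a common scale for FC and Cryo.
- **State** that similar levels alone do not show similar product effect.
- **Do not** widen the product analysis to all samples before a second dose, for the reason in step 5 of the working.

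The cost is a little more analysis. A5 results and doses drive treatment and product units are already an outcome, so little or no new data are needed. Three limits should be stated. Cryo grams are nominal, because content per unit varies. The increment covers only patients who receive a first dose and have a post-dose sample. If Cryo takes longer to give, the interval between the two samples will be longer and include more ongoing loss, so that interval should be reported by arm. No dose or trigger changes.
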